### Data analysis

The baseline characteristics (age, sex, principal diagnosis categories, and comorbididy conditions) of intervention and control subjects will be recorded and compared between groups using Chi-square tests or Fisher Exact tests where appropriate. We will also use t-tests for comparison of continuous variables. The same statistical tests will be used to compare outcomes between the two groups. Chi-square and Fisher exact tests will be used to compare the frequency of dichotomous outcomes (i.e., death or readmission, adverse events, adverse drug events). For the subset of patients who are readmitted in the two groups, we will use t-tests to compare the time-to-readmission of patients and patient health status (HUI3 overall scores) in the intervention *versus* control groups. A Kaplan-Meier analysis with log-rank test will be used to perform a time-to-event analysis in all subjects. For the economic evaluation, total costs of care and outcome events will be calculated for each arm of the trial. For each outcome, the cost difference between arms will be divided by the benefit difference to result in cost to benefit ratio.

The analysis will be performed by intention-to-treat. Patients will be analyzed in the group to which they were randomized, even if the summary of their hospital stay is generated using a communication method that differs from their group assignment. CONSORT reporting guidelines (
http://www.consort-statement.org) will be used to diligently track and report treatment crossovers and losses to follow-up through a progressive flow-chart. We will work diligently during the course of the study to limit the frequency of such occurrences. This will be achieved by a system of clear labeling of patient charts immediately after random allocation so that the care team will be aware of the assigned summary of care communication method. Research associates affiliated with the study will also be present among the clinical care team daily to reinforce the issue of compliance to patient assignments.

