**Figure 3 F3:**
[figure not shown]
Existing health issues off of a test patient from the seamless transfer-of-care tool.

Upon admission to the MTU, the research team will approach the patient for consent and will collect baseline data including socio-demographic information, co-morbidities (using the Charlson co-morbidity measurement method
[21]), and current health status using the Health Utilities Index (HUI)
[22,23]. A chart review will be conducted on each patient. This information will be collected on a secure, web-based program that was developed by the University of Calgary’s new Clinical Trial Research Unit (CRU). The CRU has also generated a web-based method for random allocation of patients to intervention *versus* control. Randomization will be requested from the investigators, and will be entirely concealed from the researchers. Randomization will be performed within 48 hours of patients leaving hospital rather than at the time of them leaving due to the nature of the MTU in which, decisions about when patients can leave often occur without much notice and residents often do not have time to complete a summary immediately given competing clinical activities. To ensure that patients will be leaving the hospital with either a copy of the completed summary produced by the TOC tool or, conversely, a hand written note for the control group, the summaries will be started by providers some time prior to the patient leaving. Figure
4 provides a summary of this process.

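### Prespecified adjustment for baseline values already collected would add precision to death or readmission and to HUI3 at almost no cost, provided HUI3 is compared in all randomized patients

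*Protocol article*

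**What the plan says.** The Data analysis section of the protocol article names its tests. Baseline characteristics (age, sex, principal diagnosis category, comorbid conditions) are to be "recorded and compared between groups using Chi-square tests or Fisher Exact tests where appropriate", with t-tests for continuous variables. It continues: "The same statistical tests will be used to compare outcomes between the two groups". For the primary composite and the adverse-event outcomes, "Chi-square and Fisher exact tests will be used to compare the frequency of dichotomous outcomes". For HUI3 the sentence opens "For the subset of patients who are readmitted in the two groups" and goes on "we will use t-tests to compare the time-to-readmission of patients and patient health status (HUI3 overall scores". A Kaplan-Meier analysis with a log-rank test covers all subjects. No regression model, covariate or baseline term is named for any outcome.

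The Study design section has the research team collect sociodemographic data, Charlson comorbidity "and current health status using the Health Utilities Index (HUI" on admission. Randomization follows later, within 48 hours of leaving hospital. Baseline measures lists age, sex and admission diagnosis. Outcome measures repeats the Health Utilities Index at 1 and 3 months. The sample size section sizes HUI3 as a comparison of two independent means (difference 0.03, SD 0.20), making no use of the baseline score.

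**The concern.** The trial measures variables that plausibly predict its outcomes, including the same HUI instrument before and after discharge, but uses none of them in the treatment comparisons. There is little power in reserve: the target of 700 per group is 2% above the 686 needed for the composite (700/686 = 1.020) and 0.4% above the 697 stated for HUI3 (700/697 = 1.004). HUI3 depends on telephone contact at 1 and 3 months, so some loss is likely.

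Two further points come from the same paragraph. The HUI3 t-test is attached to patients who are readmitted, a group formed after randomization and far smaller than the one used for sizing. And significance tests between randomized arms at baseline check a hypothesis that proper randomization makes true, so they say nothing about the treatment effect.

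**Working it through.** **Inputs from the sample size section:** event rates 0.25 and 0.1875; two-sided alpha 0.05; power 0.80 (printed as beta = 0.80; the stated 686 reproduces on the reading that this means power); 700 enrolled per group; HUI3 difference 0.03, SD 0.20.

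**Assumed, because the protocol gives neither:** R², the share of variance in the composite explained by baseline covariates, and r, the correlation of baseline with follow-up HUI3. Ranges are shown. Completion below 100% is also an assumption.

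**1. The plan's own sizes.**

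Composite, pooled variance, mean rate 0.21875: n = [1.960·√(2·0.21875·0.78125) + 0.8416·√(0.25·0.75 + 0.1875·0.8125)]² / 0.0625² = [1.960·0.5846 + 0.8416·0.5830]² / 0.003906 = 685.6, so 686. This matches exactly.

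HUI3: n = 2·0.20²·(1.960 + 0.8416)² / 0.03² = 697.7, so 698 against the stated 697, a rounding difference.

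Both are unadjusted calculations. At 700 per group their power is 80.8% and 80.1%.

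**2. Composite with adjustment.** For a standardized risk difference, variance is multiplied by about (1 − R²), so 700 per group acts like 700/(1 − R²).

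| Assumed R² | Effective n per group | Power |
|---|---|---|
| 0 | 700 | 80.8% |
| 0.03 | 722 | 82.0% |
| 0.05 | 737 | 82.8% |
| 0.10 | 778 | 84.7% |

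In a simulated logistic risk score at 25% prevalence, R² of about 0.03 and 0.10 correspond to c-statistics of about 0.61 and 0.70.

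**3. HUI3 with ANCOVA, all randomized patients.** Residual SD = 0.20·√(1 − r²); SE = SD·√(2/n); power = Φ(0.03/SE − 1.960). Example with r = 0.5 and n = 700: SD = 0.1732, SE = 0.00926, 0.03/SE = 3.240, power = Φ(1.280) = 90.0%.

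| Assumed r | 700 per group | 630 per group (90% completion) |
|---|---|---|
| none (t-test) | 80.1% | 75.9% |
| 0.3 | 83.7% | 79.7% |
| 0.5 | 90.0% | 86.7% |
| 0.7 | 97.6% | 96.1% |

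**4. HUI3 as worded, readmitted patients only.** At the design rates, 700·0.25 = 175 and 700·0.1875 = 131. These are rates for death or readmission, so the readmitted alone can be no more numerous. SE = 0.20·√(1/175 + 1/131) = 0.0231; 0.03/SE = 1.298; power = Φ(1.298 − 1.960) = 25%. With ANCOVA at r = 0.5 in the same subset, 0.03/(0.0231·0.866) = 1.499 and power is 32%. Adjustment alone does not cure the wording.

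**5. Baseline tests.** Four independent tests at 0.05 give 1 − 0.95⁴ = 18.5% probability of at least one p < 0.05 under correct randomization; ten give 1 − 0.95¹⁰ = 40.1%. Age and comorbidity are correlated, so these figures are only a guide.

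**The case against.** The strongest reply is that nothing here is an error. In an individually randomized trial of 1400 patients, chi-square and t-tests control type I error without adjustment, and for the composite the sizing and the planned test agree exactly. That stands. A reader might infer that the primary analysis is biased or invalid; the protocol does not support that reading. An analysis plan that is not shown may also contain adjusted analyses, but this article names the tests, so recommending better ones does not fault it for silence.

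Other tempting readings also fail:

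- A reader might call the baseline covariates strongly prognostic. The protocol gives no figure, and the values assumed above for the composite are modest. Baseline HUI is taken during acute illness, so its correlation with later scores could be at the low end.
- A reader might say that baseline data serve only for significance tests. HUI is not in the list of characteristics to be tested, and HUI3 supplies the utilities for the cost per QALY.
- The 2% enrolment margin matters less for the composite, which is ascertained by linkage to administrative and vital-statistics data. It bears more on HUI3.
- A reader might expect a significant baseline test to trigger adjustment. The protocol attaches no decision to those tests. They are uninformative but do not alter the treatment estimate.
- HUI3 is not named among the primary or secondary clinical outcomes, although the sample size section does size the trial for it.

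**Conclusion.** The point holds as an efficiency improvement. For the composite the gain is small: about 1 to 4 percentage points of power at 700 per group for an assumed R² of 0.03-0.10. For HUI3 it is potentially large: about 4 to 17 points at full completion for r of 0.3-0.7, and 4 to 11 points at 90% completion for r of 0.3-0.5. All of these rest on assumed prognostic strength, and the HUI3 figures also require the comparison to be made in all randomized patients. The present wording, which ties HUI3 to the readmitted subset, costs far more power (about 25% against the intended 80%) and conflicts with the sizing of 697 per group. It has to be corrected before the gain from ANCOVA can be realised.

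**What to change.** - **Primary outcome:** prespecify a logistic model for death or readmission at 3 months with age, Charlson score and baseline HUI3. Add MTU team only if it is recorded before randomization; the article does not list it among the variables collected. Report the standardized risk difference with its 95% confidence interval and keep the chi-square test as a sensitivity analysis.
- **HUI3:** analyse the 1- and 3-month scores by ANCOVA on baseline HUI3 in all randomized patients with data, and detach this comparison from the readmitted subset.
- **Covariates:** use only values fixed before randomization. Chart-review items gathered up to discharge, such as medication changes, may come later. Impute missing baseline covariates by a simple stated rule so that no patient is dropped.
- **Baseline table:** present it descriptively, without p-values.

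The cost is analysis wording and a little programming. No new patients or measurements are needed.

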### Sample size calculation and anticipated patient enrollment

As previously mentioned, a recent pilot done by the W21C team demonstrated that patients discharged from the MTU had a 23% probability of readmission to Calgary hospitals within 3 months (51 out of 219 discharged patients assessed in a pilot chart review). From this, we estimate an absolute event rate of 25% in the control group for the composite of death or readmission, and have designed our study to detect an approximately 25% relative reduction (i.e., a 6.25% absolute reduction) in the readmission rate in the intervention group. Therefore, using p_1_=0.25, and p_2_=0.1875, with alpha=0.05 and beta=0.80 in our two-tailed sample size calculation, we will require 686 patients per group. Our research plan is to enroll 700 patients per group, allowing for a safety margin for attrition. Each of the three teams usually processes an average of 2 to 4 discharges per day. As such, we anticipate that we will complete enrollment of 1400 subjects within an 18 month period and full assessment of outcomes and follow-up surveys in a 2 year period. For the secondary endpoints of post-hospital adverse events and adverse drug events, we will have adequate statistical power given that these adverse events are known to occur frequently, in approximately one quarter of patients discharged from acute-care hospitals
[1,2]. The sample size is appropriate to assess patient health status measured by HUI3 to compare two independent means for a parallel trial design, 697 patients in each group are needed to detect a clinically important difference (CID) in HUI3 overall score of 0.03 (SD=0.20).

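### The only analysis sentence that names HUI3 confines it, with time-to-readmission, to readmitted patients: a post-randomization subset that conflicts with the trial's own HUI3 sample size

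*Protocol article*

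**What the plan says.** The protocol article's Data analysis section contains one sentence that sets a population for HUI3. It opens "For the subset of patients who are readmitted in the two groups, we will use t-tests to compare the time-to-readmission of patients" and continues "and patient health status (HUI3 overall scores) in the intervention" versus the control group. By its grammar, the opening clause governs both outcomes.

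Three other statements in that section bear on the point:

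- After naming chi-square, Fisher and t-tests for baseline data, it says: "The same statistical tests will be used to compare outcomes between the two groups". This names neither HUI3 nor a population.
- On timing, it adds: "A Kaplan-Meier analysis with log-rank test will be used to perform a time-to-event analysis in all subjects".
- On principle: "The analysis will be performed by intention-to-treat".

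Elsewhere, the Outcome measures section has health status measured at baseline, 1 month and 3 months, with no limit to readmitted patients. The sample size section presents HUI3 as a calculation "to compare two independent means for a parallel trial design" and states: "697 patients in each group are needed to detect a clinically important difference (CID) in HUI3 overall score of 0.03 (SD=0.20". The Discussion lists improved health status among the questions the trial will answer.

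**The concern.** Readmission happens after randomization. It is one component of the primary composite, and the trial is designed around a relative reduction of about 25%. If the tool alters who is readmitted, the readmitted patients in the two arms are no longer alike in expectation. A difference in their HUI3 scores or their time to readmission could then reflect selection, an effect of the tool, or both, and the t-test cannot separate these.

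The second problem is one of consistency. HUI3 has its own stated important difference and a sample size that uses essentially the whole trial. Read literally, the analysis sentence uses only the readmitted minority, so it neither answers the question the calculation was made for nor has the power claimed.

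**Working it through.** **Inputs from the protocol article.** HUI3 difference 0.03, SD 0.20, 697 per group; planned enrolment 700 per group; composite event rates 0.25 (control) and 0.1875 (intervention); pilot readmission rate 23% (51 of 219), all from the sample size section. Two-sided alpha 0.05 and power 0.80 (printed under the label beta) are given there for the primary outcome and are assumed here for HUI3.

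**Step 1: reproduce the stated figure.** n per group = 2 × (1.960 + 0.842)² × SD² / δ² = 2 × 7.849 × 0.04 / 0.0009 = 697.7, against 697 stated. The figure reproduces as a comparison of all patients in two parallel groups. At 700 per group, power = Φ(0.03 / (0.20 × √(2/700)) − 1.960) = Φ(2.806 − 1.960) = 0.80.

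**Step 2: size of the readmitted subset.** The composite rates are an upper bound for readmission under the design assumptions, because some composite events are deaths without readmission: 700 × 0.25 = 175 and 700 × 0.1875 = 131. With the pilot rate and a 25% relative reduction: 700 × 0.23 = 161 and 161 × 0.75 = 121. With no effect on readmission, both arms have 161 to 175. The subset is therefore about 17% (121/697) to 25% (175/697) of the planned number per arm.

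**Step 3: power and detectable difference in the subset.** SE = 0.20 × √(1/n₁ + 1/n₂); power = Φ(0.03/SE − 1.960); difference detectable with 80% power = 2.802 × SE.

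| Scenario | Control / intervention | SE | Power for 0.03 | Detectable difference |
|---|---|---|---|---|
| Composite rates, design effect | 175 / 131 | 0.0231 | 0.25 | 0.065 |
| Pilot rate, 25% reduction | 161 / 121 | 0.0241 | 0.24 | 0.067 |
| Rate 0.25, no effect | 175 / 175 | 0.0214 | 0.29 | 0.060 |
| Rate 0.23, no effect | 161 / 161 | 0.0223 | 0.27 | 0.062 |

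The detectable difference is 2.0 to 2.2 times the stated 0.03.

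**Step 4: selection.** No arithmetic from the documents gives the bias. It depends on how the chance of having a readmission prevented varies with health status, or with how early the readmission would have occurred. The article gives neither.

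**The case against.** The strongest reply is that the sentence is badly joined and not a plan to discard most of the HUI3 data. The general sentence on comparing outcomes follows directly after the mention of t-tests for continuous variables, and HUI3 is a continuous outcome. The unrestricted measurement schedule, the 697 per group, the use of utility scores for the cost per QALY and the intention-to-treat statement all point to a whole-group comparison. This stands as far as it goes: a reader might infer that HUI3 will never be tested in all patients, and the article does not establish that. But the general sentence does not name HUI3, and the sentence that does name it restricts it. The article thus supports two incompatible HUI3 analyses.

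A reader might also infer that both subset comparisons are certain to be biased. That is too strong. If the tool has no effect on readmission, or prevents readmissions unselectively, the subsets remain comparable in expectation. Any numerical bias would rest on assumed inputs.

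Nor is readmission timing left without a sound analysis. The Kaplan-Meier and log-rank analysis in all subjects does not condition on readmission, so the defect there is confined to one additional t-test.

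Finally, the loss concerns sample size and power; nothing here shows an inflated type I error.

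**Conclusion.** The point holds as a stated analysis set that is wrong as written and inconsistent with the rest of the article. The readmitted-only comparisons are not protected by randomization and can be biased if the tool changes which patients are readmitted; size and direction are unknown. For HUI3, the literal plan has power of about 0.24 to 0.29 for the 0.03 difference instead of 0.80.

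These figures assume SD 0.20 within the subset, 700 patients per arm and a HUI3 score from every readmitted patient. Deaths and unanswered telephone surveys would lower the numbers further. The pilot rate counts readmissions to Calgary hospitals only, so 161 is a working figure and not a lower bound.

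The primary outcome of death or readmission, and the adverse-event and adverse drug event outcomes, are untouched. The point should be fixed, but it does not threaten the trial's main conclusion.

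**What to change.** In the Data analysis section:

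1. State that HUI3 overall scores at 1 and 3 months are compared between arms in all randomized patients by assigned group, preferably adjusted for the baseline HUI3 already collected. The handling of deaths and missing scores can be left to the statistical analysis plan.
2. Delete the t-tests confined to readmitted patients, or label them descriptive and draw no between-arm inference from them.
3. Name the planned all-subject Kaplan-Meier and log-rank analysis as the comparison for timing.

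The cost is a change of wording, best made before outcome data are seen. The scheduled HUI3 assessments and the planned linkage for readmissions and deaths already supply the data, and the sample size does not change.

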## Discussion

This paper outlines the study protocol for a sufficiently powered randomized controlled trial, incorporating an economic evaluation, looking at an electronic communication TOC tool developed through the partnership between Alberta Health Services, the University of Calgary, and the W21C. Since the tool is designed to transfer standardized, appropriate and accurate information in a timely manner, the study will provide evidence on how efficacious the tool will be at reducing hospital readmission, death after discharge, adverse events, adverse drug events, improving patients’ health status and its cost-effectiveness.

Randomized controlled trials (RCT) are regarded as the gold standard for clinical research assessing the efficacy of an intervention. Unlike many of the pre-post studies identified in our previously-mentioned systematic review, the present RCT is a parallel design that provides for an unbiased estimate of the effects of the intervention. Another key aspect of the present RCT is that allocation will be concealed.

Despite the obvious benefits of the parallel design with randomization, there are also some challenges. Most notably, our study design involves trade-offs between the benefits of randomizing individual patients versus the potential contamination of providers’ discharge practices when they are dealing with both the intervention and control group patients. A cluster-randomized design was considered as an approach for dealing with the latter concern. Cluster randomization has become popular in medical studies in the past two decades
[26-28]. If a cluster-randomized trial design had been chosen, each individual medical team would have been allocated to either intervention or control, instead of individually allocating patients. While using a cluster-randomization design can diminish costs and lower experimental contamination (for example, the use of the electronic discharge template by a provider to guide a dictated summary in the usual care group), this method is less efficient than individual-randomized trials as members within a cluster tend to be more similar to one another than randomly allocated participants
[26-28]. To compensate for the inefficiency of cluster-randomization, a larger sample size is required to meet statistical significance
[28]. Furthermore, there is potential for there to be between-service differences that would affect the internal validity of the study and the comparability of the intervention and control groups. Balancing these competing concerns, and in dialogue with funding agency peer reviewers, we opted for the randomization of individual patients to intervention and control to maximize the benefits of comparability between groups.

Other challenges inherent to this study relate to acute-care physician preference and familiarity with one method for generating hospital summaries over the other, and community-care physician software incompatibilities. In a few instances, acute-care physicians may have or will develop a preference of using one system over the other. This may result in a given physician not following the patient’s assigned randomization, resulting in the exclusion of the patient and a loss of that randomization. We expect to minimize this problem by continually educating and informing the physicians of the study and the importance to adhere to the randomization assignments, as well as maintaining a strong presence throughout the MTU. More so, some community-care physicians may experience accessibility issues to the TOC summaries electronic records due to software program incompatibilities. While we foresee this as a current problem, we hope that this study will encourage the implementation of compatible programs.

This study will be one of the first to have sufficient statistical power to definitively examine the important clinical outcomes of readmission, mortality and adverse events after patients leave an acute-care facility using an electronically-based TOC communication tool. The tool that we are assessing has the potential to ameliorate a vulnerable period in health care, thus enhancing patient safety and quality of care through better communication at times of transfers of care. The tool has already been pilot tested in our jurisdiction, and through this RCT is being evaluated more broadly. This study will inform our own and other health systems globally on the potential efficacy and cost implications of such electronic communication tools. Given the widespread demand and growing investments into such electronic tools (e.g., President Obama’s $19.2 billion investment into electronic health information technology
[29]) the implications of such research are truly far reaching.

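### The Discussion excludes patients whose physician does not follow the assignment, whereas the Data analysis section keeps them as randomized; both rules cannot be followed, and the exclusion could bias the primary comparison

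*Protocol article*

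**What the plan says.** Data analysis section: "The analysis will be performed by intention-to-treat". The rule that follows is "Patients will be analyzed in the group to which they were randomized". The section extends it expressly to crossovers, since it is to hold "even if the summary of their hospital stay is generated using a communication method that differs from their group assignment". It adds that the CONSORT guidelines "will be used to diligently track and report treatment crossovers and losses to follow-up through a progressive flow-chart". Charts are labelled straight after allocation "so that the care team will be aware of the assigned summary of care communication method".

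Discussion, in the paragraph on physician preference and software incompatibility: "In a few instances, acute-care physicians may have or will develop a preference of using one system over the other". The stated consequence is that a physician may not follow the assignment, "resulting in the exclusion of the patient and a loss of that randomization".

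The Participants section lists the exclusions at length. A summary produced by the non-assigned method is not among them.

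**The concern.** Both sections address one event, a summary produced by the method the patient was not assigned to. One keeps the patient in the assigned arm; the other removes the patient. A study team cannot do both, and the choice decides who is in the primary analysis.

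The exclusion would come after randomization. It would be set off by clinicians who know the allocation and are acting on a preference for one system. The Study design section notes that residents often have no time to complete a summary at discharge, so deviation could plausibly track how rushed or complex a discharge is. It could also be more common in one arm, since the two methods ask different things of the resident. If both held, the remaining patients would no longer be the groups that randomization created. The Discussion's own claim that the parallel randomized design gives an unbiased estimate would then be weakened.

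**Working it through.** **Text check.** Four questions, answered from the article:

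1. Is it the same event? Yes. Both sections speak of a method that differs from the assignment.
2. Is the handling the same? No. Data analysis retains the patient; the Discussion excludes the patient.
3. Is the exclusion limited to a per-protocol or secondary analysis? No such limit is stated.
4. Does another section settle it? No. The Participants section does not list non-adherence, and no order of precedence is given.

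**The plan's own figure.** The Sample size section gives p1 = 0.25, p2 = 0.1875, two-sided alpha 0.05 and 80% power (printed as beta), and 686 per group. With pooled variance, the mean rate is 0.21875:

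n = [1.960·√(2·0.21875·0.78125) + 0.842·√(0.25·0.75 + 0.1875·0.8125)]² / 0.0625² = (1.1459 + 0.4906)² / 0.003906 = 685.6, so 686.

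The figure reproduces. It is not in dispute; it supplies the 25% rate, the 700 planned per group and the 6.25-point target used below.

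**Illustration of possible bias.** From the document: 25% control risk and 700 per arm. Assumed, because the article gives no figures: no true effect, a fraction x excluded from the intervention arm only, and event risk r in those excluded.

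- Remaining intervention rate: p = (0.25 − x·r) / (1 − x)
- False difference: d = 0.25 − p
- Numbers analysed: n1 = 700, n2 = 700(1 − x)
- Type I error = Φ[(d − 1.96·se0)/se1] + Φ[(−d − 1.96·se0)/se1], where se0 is the pooled and se1 the unpooled standard error of the difference

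Example, x = 0.05 and r = 0.40: p = (0.25 − 0.02)/0.95 = 0.2421 and d = 0.0079. With n2 = 665, se0 and se1 are both about 0.0233. The two terms are about 0.052 and 0.011, which sum to 0.063.

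| Excluded (x) | Risk in excluded (r) | Remaining rate | False difference (points) | Type I error |
|---|---|---|---|---|
| 2%, 5% or 10% | 25% | 25.0% | 0 | 5.0% |
| 2% | 35% | 24.8% | 0.2 | 5.1% |
| 2% | 50% | 24.5% | 0.5 | 5.6% |
| 5% | 15% | 25.5% | −0.5 | 5.6% |
| 5% | 40% | 24.2% | 0.8 | 6.3% |
| 10% | 50% | 22.2% | 2.8 | 22.1% |

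The row at 15% risk shows that the bias can run against the intervention as well as for it. The last row is a deliberate extreme: 2.78/6.25 = 44% of the target difference.

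**The case against.** The strongest reply is that the operative rule is already right. The Methods state intention-to-treat without qualification and deal with crossovers explicitly. The exclusion appears in one hedged clause of a Discussion paragraph on anticipated difficulties, and it names no analysis set. An analyst would go to the Data analysis section. Preference is expected only in a few instances, and chart labelling, daily research presence and education are planned to limit its effect.

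Much of this stands. It means that the trial may well be analysed correctly, and that only one of the two statements needs to change. It does not remove the conflict. The article states no precedence, and the words describe excluding the patient, not merely a weaker contrast between methods. If study staff acted on the clause during enrolment or follow-up, the intention-to-treat commitment could be lost before any analyst saw the data. The few instances refer to physicians who hold a preference, not to a count of patients affected.

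Three stronger readings are not supported:

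- A reader might infer that the primary result would be biased. Bias requires that the clause be applied to the primary analysis, and that exclusions both differ by arm and relate to prognosis (or relate to it differently in each arm). The article establishes none of this. The only cause it names is preference, which could go in either direction.
- A reader might take 22% as the expected type I error. It comes only from the assumed extreme of 10% excluded, all in one arm, at twice the average risk.
- A reader might conclude that the power must be restated for crossover dilution, or that a complier-average analysis is required. Dilution arises under the correct intention-to-treat rule and is not a consequence of this contradiction. Adherence-based sensitivity analyses commonly belong in an analysis plan that is not shown.

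**Conclusion.** The contradiction is real and the Discussion clause is wrong as written. It conflicts with a correctly stated Methods rule on who is in the primary analysis. That conclusion rests on the text alone and needs no assumption.

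The consequence is possible bias, not certain bias, and its size and direction cannot be derived from the article. On the assumptions above it runs from nothing, through a few tenths of a point with type I error of 5.1-5.6% at 2% exclusion, to 0.8 points and 6.3% at 5% exclusion and 40% risk. The 2.8 points and 22% mark an extreme. Bias is also zero if exclusions are balanced across arms in both number and prognosis.

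**What to change.** Delete the exclusion clause in the Discussion, or reword it to match the Data analysis section. Suggested sense: *a physician may not follow the assignment; such patients are recorded as crossovers, followed through the provincial linkage, and analysed in the arm to which they were randomized.*

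State that every randomized patient, crossovers included, stays in the primary analysis. Show crossovers separately by arm in the CONSORT flow-chart that is already planned. If an analysis excluding non-adherent patients is wanted, label it as a sensitivity analysis. Instruct study staff accordingly, so that no one is dropped from follow-up for this reason.

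The cost is wording only. Death and readmission come from administrative linkage, so retaining crossovers needs no extra patient contact for the primary outcome. The 686 required and 700 planned per group do not change.
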